## Abstract

**Background:**

Scaphoid non-union results in pain and decreased hand function. Untreated, almost all cases develop degenerative changes. Despite advances in surgical techniques, the treatment is challenging and often results in a long period with a supportive bandage until the union is established. Open, corticocancellous (CC) or cancellous (C) graft reconstruction and internal fixation are often preferred. Arthroscopic assisted reconstruction with C chips and internal fixation provides minimal trauma to the ligament structures, joint capsule, and extrinsic vascularization with similar union rates. Correction of deformity after operative treatment is debated with some studies favouring CC, and others found no difference. No studies have compared time to union and functional outcomes in arthroscopic vs. open C graft reconstruction. We hypothesize that arthroscopic assisted C chips graft reconstruction of scaphoid delayed/non-union provides faster time to union, by at least a mean 3 weeks difference.

**Methods:**

Single site, prospective, observer-blinded randomized controlled trial. Eighty-eight patients aged 18–68 years with scaphoid delayed/non-union will be randomized, 1:1, to either open iliac crest C graft reconstruction or arthroscopic assisted distal radius C chips graft reconstruction. Patients are stratified for smoking habits, proximal pole involvement and displacement of > / < 2 mm. The primary outcome is time to union, measured with repeated CT scans at 2-week intervals from 6 to 16 weeks postoperatively. Secondary outcomes are Quick Disabilities of the Arm, Shoulder and Hand (Q-DASH), visual analogue scale (VAS), donor site morbidity, union rate, restoration of scaphoid deformity, range of motion, key-pinch, grip strength, EQ5D-5L, patient satisfaction, complications and revision surgery.

**Discussion:**

The results of this study will contribute to the treatment algorithm of scaphoid delayed/non-union and assist hand surgeons and patients in making treatment decisions. Eventually, improving time to union will benefit patients in earlier return to normal daily activity and reduce society costs by shortening sick leave.

**Trial registration:**

ClinicalTrials.gov NCT05574582. Date first registered: September 30, 2022. Items from the WHO trial registry are found within the protocol.

**Supplementary Information:**

The online version contains supplementary material available at 10.1186/s13063-023-07281-5.

## Background

A scaphoid fracture is the most common injury to the carpal bones. The incidence is 107–151/100.000 per year and fractures are predominantly sustained by males in their twenties [1]. Scaphoid non-union is defined as a lack of healing 6 months after injury and develops in 5–25% of cases after non-operative treatment [2, 3]. Delayed union is defined as incomplete healing 2–6 months after injury. However, some potential for a union probably exists, especially in nondisplaced fractures, otherwise this condition is associated with a transition into a persistent non-union [4]. The risk of non-union increases with delayed diagnosis and treatment, displaced fractures, proximal pole fractures, smoking, poor vascularity and advancing age [5–8].

The scaphoid is primarily covered with cartilage and has a retrograde blood supply. The dorsal branch of the radial artery accounts for 80% and a separate volar branch for 20% of the extramedullary blood supply. The proximal pole is only supplied by the intramedullary flow. Compromised blood supply can explain the potential of non-union and avascular necrosis of the proximal pole. The healing process can be complicated by volar angulation of the fracture leading to humpback deformity. This will disrupt carpal kinematics and result in lunate instability and dorsal intercalated segment instability (DISI). Untreated scaphoid non-union can lead to degenerative changes, called scaphoid non-union advanced collapse (SNAC), and irreversible impairment such as pain and altered hand function.

X-ray is commonly applied to evaluate the scaphoid, although CT scans are reportedly superior in terms of displacement, angulation and union [9]. Different measurements to describe the angulation and deformity of the scaphoid are suggested. The height length ratio (HLR) and dorsal cortical angle (DCA) (Fig. 1) are found to be the most reliable measurements [10, 11].

**Fig. 1 Fig1:**
[figure not shown]
Sagittal CT scan of scaphoid non-union. The measurement of dorsal cortical angle (DCA) and height-length ratio (HLR). The height-length ratio is calculated by dividing the scaphoid height by length

Surgical treatment of scaphoid delayed/non-union is technically demanding and often results in a long period with a supportive bandage until union is established. Current treatment strategies for delayed union and non-union include vascularized or non-vascularized bone graft with internal fixation. Kirchner wires or screws have been the gold standard for fixation. A meta-analysis found an average of 94% union with screw fixation and 77% with K-wire fixation in unstable non-union [12]. Open CC graft reconstruction is often preferred [13, 14]. However, there is an increased donor site morbidity from the iliac crest, and the outcome is not superior to distal radius C graft [15]. Arthroscopic reconstruction with C chips and internal fixation is predominantly applied in delayed union and stable non-union [16–18]. The advantages of arthroscopy include thorough wrist assessment, evaluation of concomitant ligamentous injury and minimal trauma to the ligament structures, joint capsule and the tenuous blood supply [19]. Recent studies have reported an 86–100% union rate, also in patients with cystic changes and/or translation > 2 mm, and/or humpback deformity [20–24]. A retrospective study, with 62 cases, found union in 96% arthroscopic group vs. 97% in open surgery with no difference in the functional results, however, time to union was not recorded [16]. No RCT comparing arthroscopic or conventional open C graft technique have been performed.

The objective of this study protocol is to describe the methodology for a randomized controlled trial comparing time to union and functional outcome scores of arthroscopic assisted C chips reconstruction or open C graft reconstruction for scaphoid delayed/non-union. The standard protocol items recommendations for interventional trials (SPIRIT) statement 2013 have been followed for the completion of this protocol (Additional file 1) and the items from the WHO trial registry are found in within the protocol.

### Hypothesis

Arthroscopic assisted C chips graft reconstruction of scaphoid delayed/non-union is superior to open C graft reconstruction regarding faster time to union, by at least a mean 3 weeks difference.

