## Method and analyses

### Study design

This is a single-centre, 1:1 observer-blinded randomized controlled, superiority trial. The main objective is to compare open C graft with arthroscopic assisted C chips graft reconstruction for scaphoid fractures with delayed/non-union.

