### Statistics

#### Sample size calculation

The sample size calculation was performed with an expected mean time to union of 56 days and a SD of 30 days in Group A and 77 days and SD on 40 days in group B. The sample size required in each group to provide 80% power to detect a mean 3 weeks difference [13], with two-sided alpha on 0.05, was 36 patients in each group. Considering dropouts and loss to follow-up with a rate of 20% the final number of patients needed in total for this study is 88 patients.

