#### Data analysis

Interim data analysis will not be carried out. Continuous data will be presented as means with SD or as median with interquartile range (IQR) depending on the nature of data. Categorical data will be presented as counts with percentages. Differences in demographic data and outcome measures between groups will be compared using chi-square for categorical data and Student’s *t*-test (parametric data) or Wilcoxon signed rank test (non-parametric data) for continuous data.

An intention-to-treat analysis will be conducted for the primary outcome. A per-protocol analysis will be conducted to test the non-adherence to the protocol, and patients who do not comply with the protocol will be excluded. Primary outcome will be analysed with a mixed effect model adjusted for fracture location, smoking habits and dislocation (the strata in the block randomization) to account for imbalance in baseline covariates and to improve the power of the treatment effect.

Subgroup analyses for the duration of non-union (< 6 months vs. > 6 months), patients with/without deformity based on the preoperative measurements of HLR and DCA will be performed. It will be clarified if post hoc analyses are carried out. For missing data in an outcome measure, multiple imputation analysis with the covariates: age, smoking, fracture location, dislocation > / < mm and duration of non-union will be conducted to minimize bias of nonresponse. Applied level of significance for all statistical analyses is *P* < 0.05. The statistical analyses will be performed using computerized statistical software.

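### The hypothesis claims a benefit of at least 3 weeks, but the trial is sized and tested as ordinary superiority against zero, so a significant P value alone would not establish it

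*Protocol article*

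**What the plan says.** The claim appears twice in the protocol article. The Hypothesis section says the arthroscopic technique "is superior to open C graft reconstruction regarding faster time to union, by at least a mean 3 weeks difference". The Background part of the abstract says it "provides faster time to union, by at least a mean 3 weeks difference".

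Four other sections bear on what is tested:

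- **Study design:** "This is a single-centre, 1:1 observer-blinded randomized controlled, superiority trial". No superiority margin is given.
- **Primary outcome:** no minimal clinically important difference has been established for time to union, and the authors describe their choice of 3 weeks as arbitrary.
- **Sample size calculation:** for the intervention arm the assumption is "expected mean time to union of 56 days and a SD of 30 days in Group A". The control arm, labelled group B here and Group O elsewhere, is assigned a mean of 77 days with an SD of 40. The number per group is said "to provide 80% power to detect a mean 3 weeks difference [13], with two-sided alpha on 0.05".
- **Data analysis:** a mixed effect model for the primary outcome, adjusted for the stratification factors. "Applied level of significance for all statistical analyses is" P < 0.05. The section mentions neither a shifted null nor a 3-week threshold.

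**The concern.** A hypothesis of a benefit of at least 21 days is a minimum-effect claim. To support it, the data must rule out differences smaller than 21 days. A two-sided test at P < 0.05 with no stated margin rules out only a difference of zero. The hypothesis and the stated test therefore address different questions, and the stated 80% power belongs to the second.

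The consequence is for the conclusion the trial may draw. A significant result could come with an estimate below 21 days, or with an interval reaching almost to zero. The trial would then have shown superiority without showing its own hypothesis. Conversely, a real and significant benefit of somewhat less than 3 weeks would contradict the hypothesis as worded, although it would be a positive result for a superiority trial.

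**Working it through.** **Inputs** (Sample size calculation): means of 56 and 77 days, SDs of 30 and 40 days, two-sided alpha 0.05, power 80%, 36 per group, 88 in total (44 per group). Planned difference = 77 − 56 = 21 days, exactly the minimum that the hypothesis claims.

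**1. The plan's own figure.** For a null of zero, n per group = (30² + 40²) × (z_alpha + z_power)² / 21².

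- Two-sided 0.05: 2500 × (1.960 + 0.842)² / 441 = 44.5, so 45 per group.
- One-sided 0.05: 2500 × (1.645 + 0.842)² / 441 = 35.05, so 36 per group.

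The stated 36 is thus not reproduced with the stated two-sided alpha, but it matches a one-sided test against zero. The sidedness is a separate matter. What counts here is that 36 arises with a null of zero.

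**2. Is the null zero?** The article does not write the null out, so this is an inference. If the null were a difference of at most 21 days, the planned difference would exceed it by 21 − 21 = 0. Power would equal the one-sided error rate of 2.5% at any sample size, and no finite n would give 80%. The phrase "to provide 80% power to detect a mean 3 weeks difference" therefore makes sense only against zero.

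**3. Where significance starts.** SE = sqrt(30²/n + 40²/n) = sqrt(2500/n). The smallest significant observed difference is the critical value × SE.

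| Per arm | SE (days) | Normal approximation | t distribution |
|---|---|---|---|
| 36 | 8.33 | 16.3 days | 16.6 days |
| 44 | 7.54 | 14.8 days | 15.0 days |

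All of these are below 21 days.

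**4. What a significant result would show.**

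- Observed 17 days, 36 per arm: 17 ± 16.6 gives a 95% CI of 0.4 to 33.6 days. The result is significant, but the estimate is below 21 and the interval reaches almost to zero.
- Observed 21 days, 36 per arm: 21 ± 16.3 gives 4.7 to 37.3 days (4.4 to 37.6 with the t distribution).
- Observed 21 days, 44 per arm: 21 ± 14.8 gives 6.2 to 35.8 days.

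**5. What would establish the hypothesis as worded.** The lower 95% limit must exceed 21 days. The observed difference must then exceed 21 + 16.3 = 37.3 days with 36 per arm, or 21 + 14.8 = 35.8 days with 44 per arm (normal approximation).

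**The case against.** The strongest reply is that the article explains its 3 weeks. It calls the value arbitrary, uses it to size the trial, and labels the trial a superiority trial without a margin. The intent is evidently ordinary superiority with 3 weeks as the target difference, and the hypothesis is loosely worded. This stands as a reading of intent. It is also the reason for the correction, because the sentence stating the claim under test says something else, in both places where a reader looks for it.

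A second reply is that rules for interpreting the confidence interval commonly sit in an analysis plan or full protocol, neither of which is shown. This also stands: the absence of such a rule is not the point. The point is that the hypothesis, which is fixed here, does not match the sample size and significance rule, which are also fixed here.

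A third reply is that wide intervals at borderline significance occur in any trial powered at its target difference, and that the adjusted model may change the standard error. Both are true. The thresholds above are illustrations for an unadjusted comparison under the planning SDs.

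Three stronger readings are tempting, but the documents do not support them:

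- **That no significant result could support the hypothesis.** This is true only of the P value taken alone. A 95% CI wholly beyond 21 days would support it.
- **That the plan will treat P < 0.05 as confirming 3 weeks.** No section links the two. The wording merely leaves that reading open.
- **That the hypothesis has only a 2.5% chance of being confirmed, or needs a true difference of about 44 days for 80% power** (21 + 2.80 × 8.33 = 44.3 with 36 per arm). Both figures assess a 21-day null, which the article does not propose. The 2.5% holds only if the true difference is exactly 21 days, and the 44 days holds only under the planning SDs and 36 per arm.

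**Conclusion.** The concern holds as a mismatch between the stated hypothesis and the stated test. The abstract and the Hypothesis section claim a difference of at least 3 weeks. The Study design, Primary outcome, Sample size calculation and Data analysis sections describe superiority against zero, with 3 weeks as the target difference. A significant P value alone would not establish the claim as worded, because significance starts about 4 to 6 days short of 21 (at about 16.6 days with 36 per arm and about 15 with 44).

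This rests on the planning SDs of 30 and 40 days, an unadjusted comparison of means, and the inference that the null is zero. That inference is firm, since the planned difference equals the claimed minimum. The conclusion is the same at 36 or 44 per arm. Severity is minor to moderate: the data, the model and the P value are unaffected, but what may be concluded from them is not.

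**What to change.** Make three wording changes before the data are analysed:

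1. In the abstract and the Hypothesis section, state the hypothesis as a *shorter mean time to union than open C graft reconstruction*, without the minimum of 3 weeks.
2. State that 21 days is the difference used for the sample size, chosen in the absence of an established minimal important difference.
3. State that a benefit of at least 3 weeks will be claimed only if the whole 95% CI for the difference lies beyond 21 days. Superiority itself needs no new rule, since the two-sided P < 0.05 already covers it.

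The cost is wording only, with a slightly weaker claim. This point calls for no change to the sample size or data collection. Keeping the minimum of 3 weeks as the hypothesis would instead require a test against a 21-day margin and an assumed true difference larger than the 21 days now planned.

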## Method and analyses

### Study design

This is a single-centre, 1:1 observer-blinded randomized controlled, superiority trial. The main objective is to compare open C graft with arthroscopic assisted C chips graft reconstruction for scaphoid fractures with delayed/non-union.

## Subjects

A total of 88 patients with scaphoid delayed/non-union are randomized to either:Group A – Arthroscopic assisted C chips graft reconstruction (intervention group), *n* = 44Group O – Open C graft reconstruction (control group), *n* = 44

## Inclusion criteria

Patients aged 18–68 years.A scaphoid fracture without healing 3–6 months since fracture (delayed union) for cases with either displacement > 1 mm or comminution and failed non-operative treatment.Scaphoid fracture without healing > 6 months since fracture (non-union) regardless of displacement, comminution and if previous non-operative treatment has been tried.ASA 1–3.

## Exclusion criteria

Open fracturesAssociated trans-scaphoid perilunate dislocation.Associated fracture in the hand/upper extremity.Previous failed surgical treatment for scaphoid delayed/non-union.Stage 2 SNAC or above.Avascular necrosis of the proximal pole as evaluated with MRI and absence of punctate bleeding intraoperatively.Patients with gross humpback deformity of HLR > 0.75 and/or DCA < 70°.Patients unable to understand instructions in Danish, complete the rehabilitation protocol, or answering the questionnaires because of physical or cognitive impairment, as evaluated by the surgeon at the first visit.

## Enrolment

All Danish citizens aged 18–68 years with scaphoid delayed/non-union referred to the hand surgy unit, Herlev and Gentofte University Hospital, will be offered participation in the study. Other hand unit departments in the Capital Region of Denmark will forward their referrals to our department for inclusion. The physician will review the medical records and assess whether the patients fulfil the inclusion/exclusion criteria. If the patient is found eligible, they will receive oral and written information of the study (Fig. 2) and the possibility to bring a bystander for the preparation consultation. The patients will be given a minimum of 24 h deliberation period. At the preparation consultation with the primary investigator, the patient will once again receive oral and written information, and trial risks of the study, and subsequently the consent will be obtained. The patients will simultaneously be allocated to one of the treatment groups. Patients can withdraw their consent at any time. The Helsinki Declaration will be followed [25]. The informed consent will give the primary investigator access to information about sex, age, comorbidity, trauma, time from fracture to treatment, history of smoking, occupation, hand dominance, pain, ongoing workers’ compensation and insurance claim. Baseline range of motion, grip strength, Key-pinch strength, pain in rest and activity (VAS) and Q-DASH will be recorded (Fig. 2).

**Fig. 2 Fig2:**
[figure not shown]
Schedule of study enrollment and assessment

Patients will undergo a clinical examination and CT scan of the wrist to describe angulation (HLR and DCA), displacement, localization of non-union, presence of cysts and degenerative changes. All patients with involvement of the proximal pole will undergo gadolinium-enhanced MRI to clarify vascularity, but the final assessment of avascular necrosis of the proximal pole will be performed perioperatively. If punctate bleeding after the tourniquet being off for at least 5 min of expectation cannot be visible, the patient will then be excluded from the study and will be simultaneously operated on with a vascular bone graft or a salvage procedure.

The operations will be performed at the Orthopedic Department at Herlev and Gentofte University-Hospital, Denmark, which is the largest referral hand unit in Denmark. Annually 1–25 patients are treated for scaphoid delayed/non-union. With forwarded referrals included, we estimate a 3-year inclusion period from 01–01-2023 to 01–01-2026.

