## Randomization

Based on the sample size calculation, a total number of 88 patients will be allocated into two groups of equal size.Group A – Arthroscopic assisted C chips graft reconstruction (intervention group), *N* = 44.Group O – Open C graft reconstruction (control group), *N* = 44.

The randomization is done in the outpatient clinic and the patients will be informed about the operative treatment. The randomization is done using an irreversible application in Research Electronic Data Capture (REDCap). Patients will be allocated in a 1:1 ratio by block randomization, stratified for proximal pole fracture (yes /no), dislocation (> / < 2 mm) and smoking (yes/ no). An independent statistician generated the randomization sequence for REDCap, and thus the allocation is concealed to the research staff and physicians.

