## Blinding

In this observer-blinded RCT, union is assessed by a blinded musculoskeletal radiologist. QDASH is a patient-reported survey, without the involvement of surgeons or research staff. Other secondary outcomes will be measured by an independent observer. The study will not be blinded to the operating theatre staff, surgeons, physiotherapists or patients.

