## Protocol violations and patient drop-out

The patients evaluated for inclusion will be reported in a consort diagram (Fig. 3). The statistical analysis will be conducted on an intention-to-treat basis. Outcome scores will be analysed according to the initial study group assignment regardless of possible cross-over. If crossover does occur, a secondary per-protocol analysis will be conducted.

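### Patients are randomised in the clinic but excluded during the allocated operation on an unblinded, arm-specific judgement of bleeding, which conflicts with the promised intention-to-treat analysis and can select the arms differently

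*Protocol article*

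**What the plan says.** **Allocation comes first.** Under Randomization: "The randomization is done in the outpatient clinic and the patients will be informed about the operative treatment". Under Enrolment, at the consultation where consent is taken: "The patients will simultaneously be allocated to one of the treatment groups". The REDCap allocation is described as irreversible.

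**The last eligibility check comes later.** The text following Fig. 2 says that "the final assessment of avascular necrosis of the proximal pole will be performed perioperatively". If bleeding is not visible after the tourniquet has been off for at least 5 minutes, "the patient will then be excluded from the study" and has a different procedure at the same operation.

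**The listed criterion is worded differently.** Exclusion criteria: "Avascular necrosis of the proximal pole as evaluated with MRI and absence of punctate bleeding intraoperatively". This joins an MRI finding to the finding at surgery. The text after Fig. 2 acts on the finding at surgery alone.

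**Those in theatre know the arm.** Blinding: "The study will not be blinded to the operating theatre staff, surgeons, physiotherapists or patients". Under Interventions, two surgeons do all the open operations and two others all the arthroscopic ones.

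**The analysis set.** Protocol violations and patient drop-out: "The statistical analysis will be conducted on an intention-to-treat basis". Data analysis repeats this for the primary outcome. Patients who have revision surgery stay in the study under their index procedure. No such rule covers patients excluded in theatre.

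**The concern.** A patient excluded in theatre has already been randomised. If that patient leaves the study, the set analysed is no longer the set randomised, and the comparison is protected only if both arms remove the same kind of patient at the same rate.

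Nothing in the design secures that. The finding is seen through arthroscopic portals in one arm and a direct volar exposure in the other. It is judged by different surgeons, all of whom know the arm. The debridement end-points also differ in wording: the Group A description names punctate bleeding, while the Group O description asks only for bone of healthy appearance.

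The patients at issue matter for the primary outcome. The Background lists poor vascularity and proximal pole fracture among the risk factors for non-union, so those removed are plausibly slow healers or non-healers. An arm that removes more of them would show a shorter mean time to union for reasons unrelated to the technique.

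**Working it through.** **1. Is this exclusion after randomisation?** Yes. Allocation is at the consent visit, the judgement is made during surgery, and the stated consequence is exclusion from the study. The other rules do not bring these patients back:
- The drop-out rule requires at least a 6-week evaluation, which a patient no longer followed would not have.
- Multiple imputation uses age, smoking, fracture location, dislocation and duration of non-union. It does not use the bleeding finding, so it would impute these patients as if they were otherwise similar.
- Stratification by proximal pole balances the arms at allocation, not after unequal removal. The blinded radiologist reads only those who remain.

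**2. Possible bias.** The protocol gives no exclusion rate, so these inputs are assumptions: no true difference; a share f = 0.15 of each arm are slow healers who unite D days later; all exclusions (share e of the arm) come from them. The excess mean among those retained is (f − e)/(1 − e) × D.

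- e = 0.05: 0.10/0.95 = 0.105 × D
- e = 0.10: 0.05/0.90 = 0.056 × D
- e = 0.15: 0

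| Excluded, one arm vs other | D = 21 | D = 42 | D = 56 |
|---|---|---|---|
| 5% vs 15% | 2.2 days | 4.4 days | 5.9 days |
| 5% vs 10% | 1.0 | 2.1 | 2.8 |
| 10% vs 10% | 0 | 0 | 0 |

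With 44 per arm, 5% vs 15% is about 2 vs 7 patients (44 × 0.05 = 2.2; 44 × 0.15 = 6.6). Against the 21-day target, 2.2 to 5.9 days is 11% to 28%.

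**3. Effect on numbers.** The Sample size calculation gives SDs of 30 and 40 days, so the root mean square SD is √((900 + 1600)/2) = 35.4. The stated 36 per group is not reproduced at two-sided 0.05: 2 × 1250 × (1.96 + 0.84)²/21² rounds up to 45. One-sided 0.05 gives 36. That is a separate matter, but it sets the baseline here: two-sided power at 36 per group is 71%.

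Starting from 44 per arm with 20% dropout and a share x also excluded, n = 44 × (1 − x) × 0.8:
- x = 0: 35.2 per arm, power 70%
- x = 0.10: 31.7 per arm, power 66%
- x = 0.15: 29.9 per arm, power 63%

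The loss of power is modest. Selection is the main issue.

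**4. Would counting these patients as non-united solve it?** Not as the primary analysis. Suppose only one arm detects a 15% slow group whose natural times lie between 56 + 30 = 86 and 77 + 60 = 137 days. Scoring them at 24 weeks (168 days) shifts that arm by 0.15 × (168 − 137) = 4.7 to 0.15 × (168 − 86) = 12.3 days the other way.

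On a comparison of means it also costs power. With 10% in both arms scored at 168 days, the difference becomes 0.9 × 21 = 18.9 days. The SDs become √(0.9 × 900 + 0.09 × 112²) = 44 and √(0.9 × 1600 + 0.09 × 91²) = 47. At 36 per arm, power is about 42%, against about 67% if the same 10% are excluded.

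**The case against.** The strongest defence is that avascular necrosis is a prespecified criterion, is present at baseline, is not caused by allocation, and can be confirmed only at surgery. Excluding such patients after randomisation is a recognised practice. One rule with a fixed minimum observation time applies to both arms, and in context it concerns the proximal pole, so few patients may be affected. The protocol also promises a CONSORT diagram, where exclusions by arm would normally appear, and detailed analysis-set definitions are often left to a fuller document.

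Part of this stands. The number may be small, and bias is a risk, not a certainty. But the practice is defensible when the condition is judged blind to arm and in the same way in both arms, and here neither holds. The text does not name who judges bleeding, but everyone in theatre knows the arm. A flow diagram would show unequal numbers without repairing them. Nor is this a detail left to another document: the article itself states both the exclusion and the intention-to-treat analysis.

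Three stronger readings are not supported:
- *A bias of up to 9 days, or 43% of the target.* That is 0.15 × 60 days and requires one arm to remove every such patient and the other none. Nothing in the protocol indicates that.
- *A bias favouring the arthroscopic arm.* The protocol does not show which arm would exclude more.
- *Exclusions that exceed the 20% allowance.* The protocol does not say whether they fall within it or whether excluded patients are replaced.

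**Conclusion.** The concern holds in this form: the plan removes randomised patients on an unblinded judgement made by different surgeons through different exposures. This contradicts its own intention-to-treat statement and can select the arms differently on a strong prognostic factor.

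The size is unknown because no exclusion rate is given. About 2 to 6 days of false difference against 21 days is an illustration. It rests on a 15% share of slow healers, 5% vs 15% exclusion, and healing 21 to 56 days later. It shrinks to zero as the rates become equal, and either arm could benefit. The point deserves correction despite that uncertainty because the data are hard to recover if excluded patients are not followed.

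A reader might infer that scoring these patients as failures is the natural remedy. It is not suitable as the primary analysis, because it turns the same unblinded judgement into an outcome.

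**What to change.** 1. Replace exclusion from the study with retention. Every randomised patient stays in follow-up on the same CT schedule and in the primary intention-to-treat analysis by allocated arm.
2. Use the observed time to union whatever procedure was received, and treat those not united by 24 weeks as censored. This needs a method that accepts censoring. State in advance how a patient is handled if a salvage procedure leaves no union to assess.
3. As sensitivity analyses only, analyse the set without these patients and the set counting them as failures of the index procedure.
4. Report the number found without bleeding by arm and by surgeon.
5. Reconcile the Exclusion criteria (MRI finding and absent bleeding) with the text after Fig. 2 (absent bleeding alone). As written they define different groups.

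Clinical treatment of these patients need not change. Randomising only after vascularity is confirmed would also remove the problem, but under this protocol bleeding is seen through an exposure that already belongs to one of the two treatments.

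The cost is protocol wording, follow-up of a few extra patients, and some loss of precision from retaining slow healers. The estimate then describes allocation to a technique, including any change of procedure in theatre.
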